### Blinding

All patients, all caregivers and embryologists at the clinical departments will be blinded to trial intervention allocation. This is possible because ampoules of drug/placebo will be prepared and coded in a undistinguishable way by the local central pharmacy of the Fondazione IRCCS Ca′ Granda according to a computer generated random list. The pharmacy will reveal the content of administered ampoule only after cycle completion.

The allocation sequence will be implemented through administration of anonymized ampoules in the progressive order they are coded by the pharmacy.

The progress of the study will be periodically monitored by an external monitor in order to verify the strictness of the data management. The medical doctors evaluating the main outcome will also be blinded to the trial intervention allocation. Unblinding will be possible after the embryo transfer procedure. In case of adverse effects of vitamin D supplementation, as reported by participating women, the care giver of the patient can obtain information on the participant’s allocated intervention asking to the principal investigator who will ask the pharmacy using a specific module.

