### Interventions

#### Experimental design aim 1

Recruited women will be given the drug (either 600,000 IU of 25-OH-vitamin D or placebo in a single oral administration) at the time of randomization, thus 2–12 weeks prior to oocyte retrieval and managed according to a standardized clinical protocol of ovarian stimulation with in vitro fertilization (fresh cycle). Administration of the drug/placebo will be performed by the physician in order to guarantee a compete adherence to the protocol. No dose changes are foreseen. Patients will be asked to avoid further consumption of vitamin D after randomization.

Women whose cycle will be cancelled will not be excluded (intention to treat analysis). A specific software will establish the randomization list. Sun exposure during the study period will be recorded but it will not be a reason for drop-out. Serum 25-OH-Vitamin D will be reassessed at the time of hCG administration or, if the cycle will be cancelled, at the time of the decision to interrupt the treatment. The quantitative detection of total serum 25(OH) D levels will be performed using a commercially available kit based on a chemiluminescence technology (DiaSorin) with intra- and interassay coefficients of variations equal to 10 and 15%, respectively.

Patients will be treated according to standard IVF protocols as described elsewhere [12, 13]: since neither the clinicians nor the recruited women will be aware about vitamin D dosage, clinical management of ovarian stimulation will not be conditioned by the study.

In case of supernumerary oocytes or embryos deriving from the fresh cycle, the subsequent embryo transfer using thawed embryos or oocytes will be considered for the study outcome if performed within 4 months from oocyte retrieval and 25(OH) D serum levels will be reassessed.

Serum hCG assessment to detect pregnancy will be performed at + 14/+ 16 days after hCG administration. If positive, women will undergo a transvaginal sonography 3 weeks later.

Clinical pregnancy (primary outcome) is defined as the presence of at least one intrauterine gestational sac with viable foetus.

Dates of the study: 27/06/2016–26/06/2019

A schedule of enrolment, interventions and assessments of the study protocol is reported in Fig. 1.

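### The plan gives two unreconciled times for disclosing allocation, and one permits disclosure before the cumulative primary outcome is complete

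*Protocol article*

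**What the plan says.** The Blinding section of the protocol article states who is blinded: "All patients, all caregivers and embryologists at the clinical departments will be blinded to trial intervention allocation". It adds: "The medical doctors evaluating the main outcome will also be blinded to the trial intervention allocation".

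The same section gives two disclosure times. One is restrictive: "The pharmacy will reveal the content of administered ampoule only after cycle completion". The other is permissive: "Unblinding will be possible after the embryo transfer procedure". Neither says who is told, and neither refers to the primary outcome. Unblinding after a reported adverse effect has its own sentence and its own route through the principal investigator and the pharmacy.

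The Interventions section (aim 1) defines the outcome: "Clinical pregnancy (primary outcome) is defined as the presence of at least one intrauterine gestational sac with viable foetus". The pregnancy test is set 14 to 16 days after hCG administration, and then: "If positive, women will undergo a transvaginal sonography 3 weeks later". A later transfer of thawed embryos or oocytes "will be considered for the study outcome if performed within 4 months from oocyte retrieval". The Abstract and the Aim section call the primary outcome cumulative.

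**The concern.** A cumulative outcome is not complete when the fresh embryo is transferred. The scan is still to come, and for women with stored embryos or oocytes so are further transfers that count. A blind that may lift from the transfer onwards does not cover the whole period in which the outcome is generated.

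Two decisions remain open in that period. The first is whether, and how soon, a thawed transfer is done inside the 4-month window, which is partly at the discretion of the clinician and the woman. The second is vitamin D use outside the trial. Women are asked to avoid it after randomization, but a woman who learns that she had placebo has a reason to start before a transfer that still counts. If either differs by arm because the arm is known, the comparison of cumulative rates is no longer protected by blinding, and analysis cannot restore it afterwards. The Interventions section itself relies on clinicians and women being unaware to argue that ovarian stimulation will not be influenced. Decisions on thawed transfers come after stimulation and need the same protection.

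**Working it through.** **1. Timing of the scan.** Inputs, both from Interventions (aim 1): pregnancy test 14 to 16 days after hCG administration; scan 3 weeks (21 days) after a positive test.

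- Earliest scan: 14 + 21 = day 35 after hCG administration.
- Latest scan: 16 + 21 = day 37.

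The transfer comes before the test that detects its result, so the scan falls more than 21 days after the transfer. A closer figure needs two intervals that the article does not give. Assume retrieval 1.5 to 2 days after hCG administration and fresh transfer 2 to 6 days after retrieval:

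- Shortest gap: 35 − (2 + 6) = 27 days.
- Longest gap: 37 − (1.5 + 2) = 33.5 days.

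On those assumptions, disclosure is permitted about 4 to 5 weeks before the result of a fresh transfer is established.

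**2. Timing of thawed transfers.** These count if done within 4 months of retrieval. The scan after a transfer late in that window falls more than 3 weeks later still, so the outcome can be completed after the window has closed.

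**3. The two disclosure sentences side by side.** Each can be read in two ways.

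| Reading of the disclosure time | Before the scan for that transfer? | Before counted thawed transfers? |
|---|---|---|
| After transfer, meaning the fresh transfer | Yes | Yes |
| After transfer, meaning the last counted transfer | Yes | No |
| End of cycle, meaning the pregnancy result of the fresh cycle | No | Yes |
| End of cycle, meaning all counted transfers and their results | No | No |

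Only the last reading keeps the blind until the primary outcome is complete. The first is the natural reading of the permissive sentence, because Interventions describes a fresh cycle and treats thawed transfers as subsequent to it.

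**4. Size.** If allocation were known to all concerned, the shift in the difference between arms through thawed-transfer use would be

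shift = s × d × p,

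where s is the share of women not pregnant after the fresh cycle who hold stored embryos or oocytes, d the difference between arms in use within 4 months, and p the success rate per thawed transfer. The article gives none of the three. To show the scale only, assume s = 20% to 40%, d = 10 to 30 points and p = 25%:

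- Smallest: 0.20 × 0.10 × 0.25 = 0.005, or 0.5 points.
- Largest: 0.40 × 0.30 × 0.25 = 0.030, or 3 points.

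The planned difference is 10 points (20% to 30%, Sample size calculation). The upper end is generous: with s = 40% and p = 25%, full use of stored material would add 0.40 × 0.25 = 10 points, half of the expected 20% control rate. If few women are told their arm, the shift tends to zero. This is an illustration of scale and not an estimate.

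**The case against.** The strongest reply is that the restrictive sentence governs, since the pharmacy holds the code. The Data collection and analysis section plans an interim analysis of clinical pregnancy rates on 315 completed cycles, so a completed cycle there must already have a pregnancy result. On that usage disclosure would follow the scan. This is a fair reading and it weakens the point about the scan. It does not settle whether a completed cycle includes the thawed transfers, and it leaves the permissive sentence standing at a different time.

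Second, the permissive sentence says only that unblinding is possible. A reader might infer that every woman is routinely unblinded straight after transfer; the text does not say so. It might belong with the adverse-effect procedure described next, but it carries no such condition.

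Third, a reader might infer that the blinding of outcome assessors is flatly contradicted, or that all the scans are biased. The documents do not support this. Allocation could be given to others while the assessors stay blinded, and Data collection and analysis describes the outcome as standardized and objective. Bias in reading the scan is therefore likely to be small.

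Fourth, outside vitamin D use is partly covered: women are asked to avoid it, and 25(OH)D is measured again for thawed transfers. That may detect such use but does not prevent it.

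Finally, a reader might infer that staff could tally results by arm as codes are released one at a time. The article does not say that codes are released to staff in that way, so the point does not rest on it.

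**Conclusion.** The point holds as a defect in the disclosure rule. Two times are given and not reconciled. One of them permits disclosure before the scan that defines clinical pregnancy and, if it means the fresh transfer, before thawed transfers that count. The exposure that matters is the discretionary use and timing of thawed transfers, and vitamin D use outside the trial, once patients or treating clinicians know the arm.

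The size and direction of any bias cannot be derived from the document. The range of 0.5 to 3 points in the working depends wholly on assumed inputs and on wide disclosure, and should not be cited as the expected bias. No sample size figure changes. The correction is still worth making, because it protects the primary endpoint of a trial presented as double blind and costs very little.

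**What to change.** Replace the two disclosure sentences in the Blinding section with one rule, for example: *Allocation is not routinely revealed to patients, caregivers, embryologists or outcome assessors before the woman's last counted outcome has been recorded, that is, until her 4-month window has closed and every counted thawed transfer has been assessed; preferably it is not revealed before database lock. Individual unblinding for adverse effects follows its separate procedure and is logged.*

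The minimum needed to close the gap is the per-woman condition. Waiting for database lock is a stricter preference, simpler for the pharmacy to apply.

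The cost is a change of wording and an instruction to the pharmacy. Women learn their allocation later. The adverse-effect route is unchanged apart from the log.

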### Consent

Women eligible for the study will be referred by care providers to a member of the research team who will describe the informed consent process. Details of the study will be explained to patients, including its main aims, procedures, temporal commitment, possible discomforts and risks, benefits. Recruitment will be on a voluntary basis with the right to withdraw from the study at any time; moreover, women will be informed that the decision to join the study protocol will not affect their future treatments. Volunteers will sign the informed consent after giving them the opportunity to put questions and enough time to consider their participation.

### Confidentiality

Recruited patients will be assigned anonymous codes and data analysis will be performed on anonymized datasets. Patient data collected during the study protocol will be treated in accordance with the Italian 196/2003 Data Protection Act. Electronic datasets will be accessed through a personal password; paper documentation will be accessible only to study investigators. Study data will be kept for at least 10 years after publication of study results.

## Discussion

For the most part, vitamin D is derived from the conversion of pro-vitamin D under the essential effect of solar ultraviolets. This particular mean of actually satisfying our needs represents an important concern. The mutated habits of humans in Western Worlds is not compatible with an adequate exposure to sunlight and thus hamper the provision of sufficient vitamin D [2].

The effect of vitamin D supplementation in women belonging to infertile couples has been insufficiently explored yet, although several groups have highlighted better chances of pregnancy in women replete for serum vitamin D [6]. Therefore, the hypothesis that vitamin D supplementation could improve IVF results deserves further consideration.

The present study can potentially influence the clinical practice of infertility treatment. Vitamin D insufficiency can be simply overcome. Supplementation with vitamin D is economic, simple and effective and would represent an innovative and simple adjuvant treatment of IVF with the potential additional benefit of improving the chances of natural conception. Of further relevance here is that vitamin D supplementation is free of relevant side effects.

Dosage of supplementation was based on previous data showing that a single 600.000 IU dose of cholecalciferol is able to rapidly increase serum 25(OH) D levels and to maintain adequate levels up to 90 days after administration in young subjects, including patients with severe vitamin D depletion. The proposed dosage is indeed considered safe since it gives peak levels well below the widely accepted toxic blood levels of 200 ng/ml [21, 22]. Of note, the single dose administered in-office by the physician guarantees a total adherence to treatment. However, given the lack of causal relationship between vitamin D levels and IVF outcomes and the risk of excessive vitamin D serum levels, patients will be asked to avoid further consumption of vitamin D after randomization. Moreover, at a molecular level, our analysis can provide preliminary data on reproductive cells that can be influenced by circulating vitamin D levels (endometrium, follicle, oocyte cumulus-oocyte complex). Whether the effect of vitamin D in human reproduction is mediated at ovarian, endometrial or both levels represents a matter of controversy. According to our prospective cross-sectional study aiming at investigating IVF outcomes in women with deficient 25(OH) D level, the number of top quality embryos and, as a consequence, the rate of women reaching the stage of blastocyst transfer was higher in women with sufficient levels of serum 25(OH)D. The chances of embryo implantation were also enhanced supporting the idea that the impact of the compound might be exerted in both the reproductive tissues [7]. Disentangling the potential role of vitamin D in the endometrium is particularly relevant given the key role of uterine factors in determining the outcome of IVF treatment, the significant gaps in our knowledge of mechanisms underlying endometrial-embryo asynchrony and most of all, the lack of relevant modifiers of endometrial receptivity status [23]. Also of particular note, there is growing and consistent evidence that vitamin D supplementation may improve birth outcomes and prevent some relevant obstetrics complications. According to a recent systematic review of the randomized studies on vitamin D supplementation, the compound increases mean birth weight of 58.33 g (95%CI 18.88–97.78 g) [24]. Moreover, a lower risk in pre-eclampsia was observed in those women receiving vitamin D supplementation, especially if they received also calcium [25].

Some limitations of our study should be acknowledged. Firstly, it has to be pointed out that the decision for a single dose of 600.000 IU is a pragmatic choice and remarkably simplifies our study design. Moreover, if significant benefits will emerge, this modality could easily enter clinical practice (considering also the low costs) and a high adherence can be expected. On the other hand, a non-significant result will not be a definitive reason to abandon the studies on vitamin D supplementation prior to IVF because one could argue that a more steady and constant administration (such as 2.000 IU daily) could be more beneficial. Secondly, the duration of vitamin D supplementation prior to IVF can be an additional reason of concern, in particular considering that we allowed for a certain variability between Vitamin D administration and the initiation of the cycle (2–12 weeks). In fact, folliculogenesis has been claimed to last 5–6 months and our protocol does not allow us to entirely cover this long period. Our protocol actually consents to properly test the effects of vitamin D on endometrial growth (a menstrual flow will systematically occur after the administration) and on final follicular growth (from dominance to ovulation) but not on the full folliculogenesis process. Again, we decided to privilege pragmatism and simplicity with the aim of facilitating future clinical use but, again, we have to admit that this choice can expose our results to some criticisms if no significant difference will emerge. Thirdly, we will request recruited women to avoid vitamin D consumption but we cannot request them to avoid sun exposure during the whole period of the IVF cycle. Even if one has to expect a similar frequency of this situation in the two study arms, this potential confounder might partly dilute the potential benefits of the tested supplementation of vitamin D. On the other hand, again, we opted for a pragmatic study and this confounder would just reflect real life situations. Fourthly, the decision to focus on women with insufficient vitamin D (< 30 ng/ml) rather than deficient (< 20 ng/ml) or even severely deficient (< 10 ng/ml) could be argued. In fact, the study will be underpowered for a reliable subgroup analysis according to the magnitude of the deficiency. In other words, we will not be able to assess whether the intervention could be of value only in a selected group (in particular those with the lowest levels) rather than for the whole heterogeneous group of women with serum levels below 30 ng/ml. Fifthly, the decision to randomize even women with serum levels below 10 ng/ml could be ethically debatable because this is a condition of possible clinical relevance per se. However, it has to be underlined that there is currently no recommendation for vitamin D testing before IVF and, for this reason, we did not deem unethical to include all women with serum levels below 30 ng/ml.

Overall, despite the above-mentioned limitations of our study design, we believe that this RCT could provide clinically relevant findings, in particular if statistically significant differences in favour of the treatment arm will emerge. In fact, it can influence clinical practice. High doses supplementation with vitamin D is an extremely simple and safe intervention and, if a significant benefit will emerge, one has to expect a rapid and global spread of its use. In addition, given the low costs of the intervention (less than 10 € in Italy), the economical profile can be expected to be highly cost-effective. On the other hand, for the above-mentioned intrinsic limitations consequent to our pragmatic choices, we have to recognize that a negative finding will not definitely close the issue.

## Data Availability

The datasets used and analysed during the current study will be available from the corresponding author on reasonable request.

## Abbreviations

25(OH)D: 25-hydroxyvitamin D
a-OR: Adjusted odds ratio
ART: Assisted Reproduction Technology
CI: 95% confidence interval
CPR: Clinical pregnancy rate
IVF: In vitro fertilization
RCTs: Randomized controlled trials
SUNDRO: Supplementation of vitamin D and reproductive outcome
VDR: Vitamin D receptor
